## Abstract

**Background:**

Sexual Interest in Children (SIC) is a major risk factor for sexual offending, yet clinical trials are sparse. The present protocol outlines a randomized controlled trial (RCT) that aims to investigate the effectiveness of fluoxetine and Cognitive Behavioral Therapy (CBT) in help-seeking men with SIC.

**Methods:**

Adult men contacting the Swedish telephone helpline PrevenTell are screened for inclusion and invited to further assessment on site. One hundred and eleven men with SIC (defined as DSM-5 pedophilic disorder or hebephilia) will be randomized (1:1:1 ratio) to receive one of three interventions for 14 weeks: (1) an internet-administered psychoeducational program (iPP), (2) iPP and the addition of fluoxetine 20-40 mg or (3) iPP and the addition of internet-administered CBT (iCBT). Exclusion criteria include severe psychiatric illness, contraindicating treatment and an elevated risk of committing hands-on sexual offences. Symptom intensity is assessed at baseline, pre-treatment, every other week for 12 weeks, and post treatment. The primary outcome measure is the Sexual Interest in Children: Current Assessment Scale (SIC: CAS) that quantifies sexual behaviors associated with SIC as well as perceived distress and impairment. Secondary outcomes include measures of dynamic risk-factors for committing sexual offences.

**Results:**

The data collected during the initial 20 months of recruitment were analyzed to predict the required number of individuals to be screened and estimate the probable length of the data collection phase. As of March 2022 to November 2023, 146 men have called PrevenTell and disclosed a sexual interest in minors. Following pre-screening, 110 men were excluded from participation in the trial. Current SSRI therapy was the primary reason for exclusion (n = 24; 22%), followed by an elevated risk of committing hands-on sexual offences (n = 14; 13%). Among the 31 men who underwent the screening procedure on site, 26 were allocated to either iPP, iPP+fluoxetine, or iPP+iCBT. The recruitment rate indicates that the trial will be concluded within the pre-estimated timeframe.

**Discussion:**

This is the first RCT of treatment with SSRI and iCBT in a population of help-seeking men with SIC. The significance of this trial and its methodological strengths and limitations are discussed.

## Introduction

1

Pedophilic disorder (PeD), characterized by persistent sexual attraction to prepubescent children, is a risk factor for committing a first sexual offence as well as for recidivism (1–3). The estimated prevalence of a pedophilic sexual interest ranges between 0.3-3.8% in the adult male population, with an upper limit of 5%; the assumed prevalence in the adult female population is significantly lower (1). Sexual Interest in Children (SIC) includes pedophilic interest and interest in children who are entering puberty (ie, hebephilia) (4).

Given the considerable suffering and negative consequences associated with experiencing sexual abuse as a child, it is imperative to provide treatment to individuals at risk of committing such offences prior to their occurrence (5). The World Federation of Societies of Biological Psychiatry (WFSBP) provides guidelines for treatment of paraphilic disorders including PeD. The recommendations distinguish 5 levels of treatment depending on the risk for sexual offences, from low-risk individuals with mild paraphilic conditions to moderate and high-risk individuals and the most severe cases. The treatment algorithm includes Cognitive Behavioral Therapy (CBT) as the only intervention for mild cases (evidence level C/D), with the addition of Selective Serotonin Reuptake Inhibitors (SSRIs, eg, fluoxetine 40-60 mg/day or sertraline 200 mg/day, evidence level C) as the next step if satisfactory results are not obtained. Testosterone-lowering agents should be considered for individuals with moderate to high risk of committing sexual offences (6). Studies suggest that these agents reduce paraphilic sexual fantasies and outlet as well as the risk for committing Child Sexual Abuse (CSA) in help-seeking men with PeD. However, long-term treatment has documented adverse effects (eg, weight gain, gynecomastia, and bone density reduction), which necessitate a careful clinical evaluation of the benefits and potential risks before initiation, and thereby limit their use (7, 8).

Conversely, the adverse reactions associated with SSRIs (eg, headache, nausea, fatigue) are usually milder and typically decrease over time (9). Impaired sexual functioning is, however, a commonly reported adverse effect related to SSRI therapy and less likely to be transient; numerous studies suggest that more than 25% of individuals taking SSRIs experience sexual dysfunction as an adverse effect (10). When SSRIs are used to regulate problematic sexual behaviors, these agents significantly reduce desire for sexual behavior such as (1) frequency of masturbation and pornography use in non-offending men with compulsive sexual behaviors (11); (2) self-reported sexual behaviors in sexual offenders (12); and (3) self-reported frequency of unconventional sexual behaviors in men with paraphilic disorders (13).

The rationale for treating paraphilic disorders with SSRIs is based on the finding of reduced libido, as well as the beneficial effect on common psychiatric co-morbidities (eg, anxiety and depression). Moreover, it has been proposed that SSRIs may have a positive impact on the regulation of impulsive behavior (6).

Regarding studies specifically focused on examining the efficacy of SSRIs in the treatment of SIC, Winder, et al. (2014) conducted a trial in which men convicted of sexual offences (n = 49) (all but one convicted of child sexual abuse) were treated daily with fluoxetine 20-60 mg (n = 36), cyproterone acetate (CPA) 50-100 mg (n = 5), a combination of fluoxetine and CPA (n = 7) and a gonadotropin-releasing hormone agonist (n = 1). Results showed that all outcome measurements (sexual preoccupation, sexual compulsivity, and hypersexuality) were significantly reduced after 4 months of treatment in both the fluoxetine group and the anti-androgen group (14). In a retrospective study, Greenberg, et al. (1996) found a significant decrease in the severity of sexual fantasies in men (n = 58), of whom 71% were diagnosed with pedophilic disorder, after they received treatment with fluvoxamine, fluoxetine, or sertraline. During the 12-week study period, the fantasy severity decreased significantly between baseline and week 4, and between week 4 and week 8. There were no significant differences observed between the three SSRIs in terms of efficacy or reported adverse reactions (15). Additional support for the utilization of SSRIs in SIC is found in case studies (16, 17) however other case reports found that fluoxetine treatment did not lead to a significant change in pedophilic fantasies (18, 19).

None of the trials used a main outcome measure specifically assessing the change in behaviors associated with SIC and the study designs limit the conclusions that can be made. Research indicate that SSRI treatment could be a viable treatment option for the management of paraphilic disorders (20). To the extent of our knowledge, no randomized controlled design trial has evaluated SSRI treatment of SIC.

Although existing evidence indicates that treatment is generally effective in reducing sexual crime recidivism, the outcomes of psychological treatment programs specifically targeting child sexual offenders are less conclusive (21, 22). There is currently no firm evidence that psychological interventions reduce sexual re-offending in this subgroup (23). Regarding preventive psychological interventions, the German Preventive Project Dunkelfeld provides treatment to help-seeking at-risk individuals with SIC. In a non-randomized wait-list control evaluation of the psychological treatment program, treated individuals (n = 56) were compared to controls (n = 22) on pre-post self-report measures. The results suggested significant reduction in several dynamic risk factors for sexual violence (eg, offence-supportive attitudes and sexual dysregulation) (24). However, the robustness of the findings has been discussed and the statistical methods used in the original study have been criticized (25). In 2022, Lätth et al. published the results of a study which randomized individuals (n = 160) who used child sexual abuse material to receive either internet-delivered Cognitive Behavioral Therapy (iCBT) (n = 80) or a psychological placebo intervention (n = 80). Participants were anonymous and recruited from forums on Darknet. Results showed a significant decrease in viewing time, severity of content, and related behaviors in the active treatment group as well as support for the feasibility and safety of the treatment program (26).

In this trial, all participants receive psychoeducation – interventions provided to educate individuals about the nature of their disorder or illness. Psychoeducation has been proposed to reduce risk of relapse in patients with schizophrenia (27) and depression (28). However, the evidence for psychoeducation as a treatment intervention is limited by weak study designs and the fact that the concept itself is poorly defined. As Compulsive Sexual Behavior Disorder (CSBD), personality disorders, depression, and anxiety are common in men with SIC, the psychoeducational program used in this trial will not only address problematic sexual interests but also take common psychiatric comorbidity into account (29, 30).

Findings from preventive interventions show that a subpopulation of men at increased risk of committing sexual offences against children seek therapy (31, 32). This observation reveals an opportunity to proactively intervene before offences occur. The importance of developing evidence-based treatments for help-seeking men with SIC has been repeatedly emphasized. There is nevertheless a crucial lack of high quality trials (33). This protocol outlines the method and intervention framework for a randomized add-on-controlled trial evaluating treatment with fluoxetine and iCBT for help-seeking men with SIC, as well as preliminary results regarding feasibility.

### Aim

1.1

#### Primary objectives

1.1.1

The primary objective of the trial is to examine whether add-on therapy with fluoxetine or iCBT is more effective than a standalone psychoeducational program for the reduction of problematic sexual behaviors in help-seeking men with SIC.

#### Secondary objectives

1.1.2

The secondary objectives include an investigation of whether add-on therapy is more effective than a psychoeducational program given alone for the reduction of (1) symptoms of psychiatric comorbidity, (2) perceived loneliness and improving quality of life, and (3) cognitive distortions and emotional congruence with children. For an account of all secondary objectives, see **Table 1**.

**Table 1 T1:** Secondary objectives of the PARACHUTES trial.

Baseline
1. To investigate clinical and sociodemographic parameters associated with SIC.
2. To investigate biological markers associated with SIC.
Evaluation of treatment interventions
1. To evaluate whether add-on therapy with fluoxetine or iCBT is more effective than a standalone psychoeducational intervention to: (a) Reduce symptoms of psychiatric comorbidity. (b) Reduce perceived loneliness and improve quality of life. (c) Reduce cognitive distortions and emotional congruence with children.
2. To assess for any differences in drop-out rate and adherence between the treatment groups.
3. To assess adverse effects (fluoxetine) and negative effects (iCBT/iPP); to investigate any links between drop-out rates, reported adverse effects, and/or efficacy.
4. To compare any difference in treatment satisfaction between the treatment groups.
Evaluation of treatment (general)
1. To investigate whether there are any indications that clinical, psychosocial, or biological factors can predict treatment response, drop-out rate, and adherence to treatment.

## Methods

2

### Design

2.1

The present clinical trial is an open randomized controlled add-on trial. Subjects will be randomized to one of the following conditions: (1) an internet-administered psychoeducational program, iPP (control intervention), (2) iPP and fluoxetine 20-40 mg daily (experimental intervention), or (3) iPP and iCBT (experimental intervention). The design controls for expectations of seeking treatment and participation in a trial, attention from the research team, and contact with a psychologist. The primary endpoint is at week 14. All participants will be encouraged to continue treatment after completing the trial procedures. Those randomized to the control intervention will be offered the iCBT program and pharmacological treatment if clinically warranted after the trial period **Figure 1** presents a CONSORT diagram illustrating each stage of the trial.

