#### The internet-administered psychoeducational program

2.6.1

The program comprises 4 text modules which include information on paraphilic disorders and CSBD, depression, anxiety and crisis reactions, the consequences of being subjected to child sexual abuse, and the legal measures in Sweden aimed at safeguarding minors from such abuse (for a description of the contents, see **Table 3**). The program does not contain behavioral interventions or modification strategies. After each module, the participants will be asked to submit reflections on the topics highlighted in the module; these will be read by a designated psychologist who will then provide feedback. The participant will have access to the program for the whole duration of the trial, however the opportunity for direct feedback from a psychologist is restricted to a period of 4 weeks.

**Table 3 T3:** Treatment content in the psychoeducational program and cognitive behavioral therapy program in the PARACHUTES trial.

	Intervention		
Treatment content	iPP	iPP + Fluoxetine	iPP + iCBT
Module 1			
Perspectives on how psychoeducation can support behavioral change	X	X	X
Information about treatment with fluoxetine		X	
Presentation of the overall treatment goals	X	X	X
Introduction to CBT			X
Worksheets:			
*Registration of problematic sexual behaviors*			X
*Identifying issues and setting goals*			X
*CBT triangle*			X
Reflection exercise:			
*Reflect on issues highlighted in the module*	X	X	
Module 2			
Description of SIC and other paraphilias/paraphilic disorders	X	X	X
Information about the consequences of victimization of sexual abuse	X	X	X
Information about why children can never give consent to sexual activity	X	X	X
Information about Swedish laws that criminalize the sexual abuse of minors	X	X	X
Worksheets:			
*Identify and challenge distorted beliefs about children’s sexuality*			X
*Registration of problematic sexual behaviors*			X
Reflection exercise			
*Reflect on issues highlighted in the module*	X	X	
Module 3			
Description of compulsive sexual behavior disorder	X	X	X
Information on the importance of consent for sexual activities between adults	X	X	X
Information about psychiatric comorbidity	X	X	X
Information about self-care interventions	X	X	X
Worksheets:			
*Registration of problematic sexual behaviors*			X
Reflection exercise:			
*Reflect on issues highlighted in the module*	X	X	
Module 4			
Identification of surpluses and deficits of sexual and non-sexual behaviors			X
Motivation			X

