#### The iCBT program

2.6.3

The iCBT program is an adapted version of an evaluated and published manual developed by the research team at ANOVA and draws on techniques from behavioral, cognitive, and third wave theoretical frameworks (39). The program comprises 10 modules administered in a fixed order and includes key features of CBT (for the contents, see **Table 3**). The contents of the treatment program specifically target the following risk factors for sexual recidivism: sexual preoccupation, sexualized coping, SIC and other paraphilias, emotional congruence with children, offence-supportive attitudes, self-regulation problems, and lack of relationships/feelings of loneliness (40, 41). Participants are expected to complete one module every week by returning homework assignments related to the topics covered in each module; a designated psychologist will give direct feedback on homework before the next module commences. All participants will have access to the program for the entire 14-week period, but access to direct support from the psychologist is limited to a period of 12 weeks.

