#### Follow-up

2.6.4

A secure web platform will be used for data collection and psychologist-participant communication. Participants will be instructed to log on to the web platform the day after randomization to access the first module of the treatment program. Every participant will be assigned an individual psychologist who will be responsible for providing feedback on reflection exercises (iPP and iPP+fluoxetine) and homework assignments (iCBT) between and during follow-up visits. Participants have the option to work at their own preferred speed during the treatment period, however they are encouraged to complete one module each week. The psychologist will be available to provide feedback via an email service on the web platform during two scheduled days each week. Participants assigned to the iPP+fluoxetine group will receive follow-up from a psychiatrist as outlined in the SPIRIT schedule shown in **Figure 2**. For all participants, the follow-up procedure consists of a phone call between day 3 and day 5, followed by a video meeting at 4 weeks, before the final visit on site at 14 weeks. Participants who are allocated to either iPP or iPP+fluoxetine receive an extra video follow-up at the 8-week mark.

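### Psychologist contact is matched in kind but not in amount between iPP and iPP+iCBT, so the Design section's claim to control for it needs narrowing

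*Protocol article*

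**What the plan says.** The Design section (2.1) claims, without qualification: "The design controls for expectations of seeking treatment and participation in a trial, attention from the research team, and contact with a psychologist".

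The sections on the interventions give the amounts:

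- **iPP (2.6.1).** "The program comprises 4 text modules", and "the opportunity for direct feedback from a psychologist is restricted to a period of 4 weeks".
- **iCBT (2.6.3).** "The program comprises 10 modules administered in a fixed order", with feedback on the homework for each module before the next begins, and "access to direct support from the psychologist is limited to a period of 12 weeks".
- **All arms (Follow-up, 2.6.4).** Each man has his own psychologist, a phone call on days 3 to 5, a video meeting at week 4 and a site visit at week 14. On written feedback: "The psychologist will be available to provide feedback via an email service on the web platform during two scheduled days each week".
- **Non-iCBT arms (2.6.4).** "Participants who are allocated to either iPP or iPP+fluoxetine receive an extra video follow-up at the 8-week mark".
- **Fluoxetine arm (2.6.4).** "Participants assigned to the iPP+fluoxetine group will receive follow-up from a psychiatrist", on a schedule given in Figure 2, which is not shown in the text at hand.

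Among its limitations, the Discussion names the open design and the lack of placebo, and notes that there is no agreed way to control for non-specific effects of psychotherapy. It does not mention the difference between 4 and 12 weeks, and it does not withdraw the Design statement.

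**The concern.** If a design controls for contact with a psychologist, the reader may rule out contact as an explanation for a difference between arms. That requires the arms to have similar amounts of contact, and on the stated figures iPP and iPP+iCBT do not.

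Three features make this matter here. The trial is open, and the primary outcome (SIC: CAS) is self-reported, so non-specific effects have a route into the result. The gap also falls inside the measurement period: if both feedback periods start with treatment, then from about week 4 to week 12 the iCBT arm has continuing feedback and the control arm does not, while symptoms are rated every other week and the model compares slopes over that time. Finally, some secondary outcomes, such as loneliness, drop-out and treatment satisfaction, could plausibly respond to personal contact itself.

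What is at stake is the interpretation of a positive iCBT result. A reader who trusts the Design sentence could credit the CBT content with an effect that is partly due to eight more weeks of support.

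**Working it through.** **Inputs.** Feedback periods and module counts come from sections 2.6.1 and 2.6.3, scheduled contacts and feedback days from 2.6.4, and the trial period of 14 weeks from the Abstract and 2.6.3.

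| | iPP | iPP+iCBT | Comparison |
|---|---|---|---|
| Weeks of direct psychologist feedback | 4 | 12 | 12/4 = 3.0-fold; 12 − 4 = 8 weeks |
| Share of the 14 weeks | 4/14 = 29% | 12/14 = 86% | |
| Modules with feedback | 4 | 10 | 10/4 = 2.5-fold |
| Possible feedback days, at 2 per week | 4 × 2 = 8 | 12 × 2 = 24 | 16 more |
| Scheduled calls, videos and visits | 4 (days 3–5, weeks 4, 8, 14) | 3 (days 3–5, weeks 4, 14) | 1 fewer |

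The feedback-day row assumes that the two weekly days apply only within each arm's feedback period. The figures describe access to feedback; contact actually received may differ. The last row runs the other way: the week-8 video gives iPP one more meeting. One meeting does not make up for eight weeks of feedback on six further modules.

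**What contact would do to the test (illustration with assumed effects).** The article does not print the variance components behind its sample size, so that figure cannot be reproduced. The SD can be back-solved from the stated target: 0.29 points per two weeks, 80% power, 0.05 taken as two-sided, 110/3 = 36.7 rounded up to 37 per arm, with the 80% read as applying to each comparison.

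- SD = 0.29 / [(1.96 + 0.84) × √(2/37)] ≈ 0.445 points per two weeks.
- SE of the slope difference = 0.445 × √(2/37) ≈ 0.104.

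Suppose CBT content had no effect and the extra contact alone produced a share *s* of the target slope. The chance of a significant difference is Φ(0.29*s*/SE − 1.96) + Φ(−0.29*s*/SE − 1.96):

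| *s* | Slope from contact | Over 14 weeks (× 7) | Chance of significance |
|---|---|---|---|
| 0 | 0 | 0 | 5% |
| 10% | 0.029 | 0.20 points | 6% |
| 25% | 0.0725 | 0.51 points | 11% |
| 50% | 0.145 | 1.01 points | 29% |
| 100% | 0.29 | 2.03 points | 80% |

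Nothing in the article says which row is realistic. The table shows only that the consequence depends strongly on a quantity the design leaves unmatched.

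**The case against.** The best defence is that the trial never set out to isolate CBT content. Its primary objective is whether adding iCBT beats psychoeducation alone. Guided iCBT includes feedback on homework, so support is part of the treatment, and randomization gives a valid estimate for that package. **This stands.** A reader might infer that the primary comparison is invalid; the documents do not support that.

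It can also be said that the Design sentence means control in kind, since every arm has a psychologist, and that the Discussion already concedes the difficulty of controlling non-specific effects. The first is a fair reading, but the sentence does not say so. The second is general and leaves the 4 and 12 weeks unmentioned.

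Other stronger readings are tempting and should be resisted:

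- *iCBT partly replaces iPP.* Table 3 does not show this. The topic of iPP module 4 reappears in iCBT modules 3 and 10, and the other iPP text topics are marked for every arm. The reflection exercises give way to worksheets, which also receive feedback.
- *The week-8 video is a further imbalance.* It goes to the arms with the shorter feedback period, so it is a partial offset.
- *Contact could explain the whole target difference.* That would need a contact effect equal to the full 0.29 points per two weeks, and no figure in the article supports one.
- *The fluoxetine contrast has the same fault.* The fluoxetine arm follows the same iPP programme with the same 4-week feedback period. Psychiatrist follow-up is described for that arm alone, but its amount is in a figure not shown, and section 2.6.2 states an aim of comparable interaction across groups. No more than that can be said.

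**Conclusion.** The concern holds for the iPP versus iPP+iCBT contrast. The Design section claims a property that sections 2.6.1 and 2.6.3 contradict in amount: 4 against 12 weeks of feedback and 4 against 10 modules, only partly offset by one video meeting. The 3-fold and 2.5-fold ratios are exact as statements of planned access. The effect of the gap on SIC: CAS is unknown, and the illustration rests on assumed contact effects and a back-solved SD.

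The trial can conclude that the guided iCBT package is or is not better than iPP alone. It cannot attribute a difference to CBT content over and above longer psychologist support. This is a fault in a stated claim and in the interpretation that it invites; the estimate for the package is unaffected.

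**What to change.** 1. **Design section.** Delete the claim on attention and psychologist contact, or qualify it, for example: *Every arm has an assigned psychologist, so contact is controlled in kind; for the iCBT comparison it is not controlled in amount or duration.*
2. **Description of the contrast.** Call it iPP+iCBT with 12 weeks of psychologist support versus iPP with 4 weeks. Keep the other contrast as iPP+fluoxetine versus iPP, and state that psychiatrist follow-up is described for the fluoxetine arm alone.
3. **Limitations.** Name the unequal psychologist contact beside the existing sentence on non-specific effects of psychotherapy.
4. **Conclusions.** Limit any iCBT conclusion to the package.
5. **Reporting.** Tabulate psychologist messages and other contacts per man by arm. Messages should be retrievable, because psychologist–participant communication runs through the web platform; calls and video meetings may have to be counted from visit records. Keep the table descriptive. Contact arises after randomization, so adjusting for it in the model would not isolate the effect of content.

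The cost is a few sentences and one table, with no change to sample size, randomization, interventions or the primary model. The downside is a narrower claim for the iCBT effect.
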